### Concomitant medications

Concomitant medication will be recorded at each visit. The participants will be immediately discontinued from the study medication if they commence any other systemic hormonal therapy (such as another form of systemic HRT or the oral contraceptive pill), any form of anti-estrogen medication or initiation of a liver-enzyme inducing agent. The medications or interventions described in Table 3 will be discouraged during the study; their use will be documented, but the participant will be allowed to remain in the study.

**Table 3 Tab3:** Concomitant medications

• Intra-articular steroid, particularly when into the hands or within 3 months of the week 24 visit • Oral steroid, particularly when for longer than 5 days consecutively or within 6 weeks of the week 24 visit • Intramuscular steroid at any point during the study • Use of intra-articular hyaluronan to a hand joint at any point during the study • New prescription of non-steroidal anti-inflammatory drugs or other analgesic, particularly when within 4 weeks of the week 24 visit • Initiation of treatment such as glucosamine or chondroitin at any point • Initiation of hand exercises or other relevant non-pharmacological therapy at any point	

### Compliance with the study medication

Clinically significant non-compliance will be defined as more than 14 days of missed medication in any calendar month, following which the participant will be withdrawn from study medication but invited to continue study follow-up.

### Breakthrough pain relief medication

Participants may experience flares of hand pain during the study. During this time, they should take their usual analgesic medications as required. If possible, no new medications should be commenced for pain in the hand or elsewhere. Where paracetamol is not usually taken already, participants will be instructed that they can use paracetamol up to 1 g four times daily for the relief of breakthrough pain if they wish, preferably avoiding taking any in the 24 h prior to a study visit. Any use of such breakthrough pain relief will be documented at each visit, and the participant asked to record this in their study paper diary.

### Statistical analysis

As this is a feasibility study not aiming to assess treatment effects but to test rates and feasibility of randomisation, a formal power calculation was not conducted. Instead we estimated 60–90 participants as the number required for the feasibility study in order to be able to accurately calculate a sample size that could detect a moderate standardised effect size of 0.3 to 0.5 in the future definitive trial [53]. Outcome data from this number of participants will be used to estimate standard deviations and confidence intervals (CIs) of the treatment estimates which will be used to inform a sample size calculation for a definitive trial.

The primary analysis will evaluate the feasibility of this study design based on the outcome measures for the primary research objectives described in Table 1: rates of eligible participants; rates of recruitment/randomisation; retention rates; and study medication compliance. These outcomes will be reported on an intention-to-treat (ITT) basis for each treatment group, with sensitivity analyses conducted on a per protocol (PP) basis. The PP population will exclude any participants with protocol deviations pre-specified in the analysis plan, such as reported non-compliance with the medication or reported concomitant medications use (as per Table 3). We will identify those who completed the study PP prior to unblinding of any analyses. Mean and standard deviation, or median and interquartile range, will be presented for continuous outcomes, depending on distribution, and numbers with percentages for binary and categorical data, for all planned primary and also for secondary outcome measures. Demographic and clinical characteristics for the two groups at baseline will be presented descriptively. Results will be reported descriptively as per Fig. 2 and in accordance with the Consolidated Standards of Reporting Trials (CONSORT) extension to randomised pilot and feasibility trials [54].

**Fig. 2 Fig2:**
[figure not shown]
CONSORT pilot and feasibility trials flow diagram schematic

The secondary objective outcome measure, average hand pain is the planned primary outcome for the future definitive trial. This outcome is scored as 0–10 on a Numerical Rating Scale and collected from participant daily pain ratings for the 14 days prior to the baseline (week 0) and the week 24 study visit. The participant preference for hand pain data collection (online questionnaire or paper diary) will be compared and reported. Average hand pain will be reported as means and 95% CI based on a multivariate linear regression model with adjustment for the minimisation factors: study site (3 levels), and pattern of involvement of painful joints (IPJ hand OA only, IPJ plus base of thumb OA, or base of thumb OA only). This will be compared descriptively with the recalled average hand pain over the last 14 days at each visit, in terms of completion rates and differences between these measures. The change in average hand pain from baseline to 24 weeks and the difference in the means together and the corresponding 95% CI will also be reported for each treatment group and overall. No formal statistical testing will be undertaken, as the study is not powered for this purpose. Additional analyses will include blood monitoring and safety data; pre-screen and screen-out rates; willingness to be randomised if eligible; and other measures of acceptability, including retention rates both overall and by recruitment site; response in those with IPJ hand OA only, IPJ and base of thumb OA, and base of thumb OA only; and those with or without evidence of radiographic hand OA. Further analysis outside of this primary analysis plan may be necessary to fully understand the feasibility of this study and to inform the future definitive trial. If this occurs, such analysis will be described in full in any results publication arising from this feasibility study. Reasons for participant unblinding; missing data; withdrawals or loss to follow-up will be carefully considered and reported by treatment group and patterns of ‘missingness’ will be explored.

Data will be analysed using an appropriate validated statistical software such as Stata, StataCorp LP, USA [55]. No comparative interim analyses will be performed. A trial statistician will contribute to the statistical aspects of the study.

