### Randomisation

Consenting, eligible participants will be randomised 1:1 to either Duavive or placebo at the baseline visit. Randomisation to the interventions will be carried out via a secure (encrypted) web-based randomisation service, the Oxford Clinical Trials Research Unit (OCTRU) Registration, Randomisation and Management of Product (RRAMP). Randomisation will be performed using a minimisation algorithm including a random element to ensure balanced allocation of participants across the two treatment groups, stratified by centre and the profile of painful joints (IPJ hand OA only; IPJ plus base of thumb OA; or base of thumb OA only) [52]. To prevent predictability, the minimisation algorithm will be seeded, randomising the first few participants using simple randomisation. Specific details will be stored within a randomisation and blinding plan, stored securely in the confidential statistical trial master file.

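### The hand-pain regression adjusts for site and joint pattern but not for the baseline 14-day pain score already collected, which costs precision and leaves a small trial exposed to chance baseline imbalance

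*Protocol article*

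**What the plan says.** All of this is in the protocol article.

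- Statistical analysis (text after Fig. 2): average hand pain is to be reported as means with 95% CIs "based on a multivariate linear regression model with adjustment for the minimisation factors". The two factors listed are study site, with 3 levels, and joint pattern. No other covariate is named.
- Same text: the score is a 0-10 rating "collected from participant daily pain ratings for the 14 days prior to the baseline (week 0) and the week 24 study visit", so a baseline value on the outcome's own scale is planned.
- Same text: a further summary covers "The change in average hand pain from baseline to 24 weeks and the difference in the means together" with a 95% CI. No baseline term is mentioned for it.
- Randomisation: allocation is by minimisation, "stratified by centre and the profile of painful joints". Baseline pain is not a factor.
- Statistical analysis (text after Fig. 2): "average hand pain is the planned primary outcome for the future definitive trial". Earlier in the section, the outcome data "will be used to estimate standard deviations and confidence intervals (CIs) of the treatment estimates", and these quantities are meant to help size that trial. The Secondary objectives also ask for an estimated effect size.

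The article does not spell out the dependent variable of the regression. I read it as the week-24 average.

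**The concern.** The baseline value of an outcome is often its best single predictor. Here it is measured before allocation and is not balanced by the minimisation. A model with only site and joint pattern leaves the variation explained by baseline pain in the residual, so the treatment CI is wider than it need be. It also leaves the single observed estimate exposed to whatever baseline difference chance produces.

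The change score does use baseline, but it fixes the coefficient at 1. If r is below 1 (with similar SDs at the two times), that over-corrects an imbalance and adds the baseline's own noise. The plan therefore offers two hand-pain contrasts, and neither is the efficient one. At stake are the effect estimate and CI that the study is meant to pass on to the definitive trial.

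**Working it through.** **The plan's own figure.** The sample size of 60-90 cannot be reproduced: the article says that no power calculation was done, and it states no SD, power or correlation. The check therefore concerns relative precision only.

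**Inputs from the article.** 60-90 participants, 1:1; site with 3 levels and joint pattern with 3 levels; target standardised effect 0.3-0.5; drop-out ceiling 30% (Data monitoring).

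**Assumptions.** r is not given and is varied from 0 to 0.7. The SD is taken as equal at baseline and week 24 and set to 1, so results are in SD units.

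**Formulas.**

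- SD relative to the week-24 score alone: √(1−r²) for the baseline-adjusted analysis and √(2(1−r)) for the change score.
- Variance of change over variance of adjusted: 2(1−r)/(1−r²) = 2/(1+r). This is 1.54, 1.33 and 1.18 at r = 0.3, 0.5 and 0.7.
- Half-width of the 95% CI without baseline: t(0.975, N−6) × √(4/N). The six parameters are the intercept, treatment, two site terms and two joint terms. The change-score half-width is this times √(2(1−r)).
- Half-width with baseline: t(0.975, N−7) × √(4/N) × √(1−r²) × √(1+1/(N−8)). The last factor is the expected price of estimating the slope.

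Example, N = 60, r = 0.5: without baseline 2.005 × 0.2582 = 0.518; with baseline 2.006 × 0.2582 × 0.866 × 1.0096 = 0.453.

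| Assumed r | Adjusted SD factor | Change SD factor | N=60: week 24 only | N=60: change | N=60: adjusted | N=90: week 24 only | N=90: adjusted |
|---|---|---|---|---|---|---|---|
| 0 | 1.000 | 1.414 | 0.518 | 0.732 | 0.523 | 0.419 | 0.422 |
| 0.2 | 0.980 | 1.265 | 0.518 | 0.655 | 0.512 | 0.419 | 0.413 |
| 0.3 | 0.954 | 1.183 | 0.518 | 0.613 | 0.499 | 0.419 | 0.402 |
| 0.5 | 0.866 | 1.000 | 0.518 | 0.518 | 0.453 | 0.419 | 0.365 |
| 0.7 | 0.714 | 0.775 | 0.518 | 0.401 | 0.373 | 0.419 | 0.301 |

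Against the week-24 score alone, adjustment narrows the CI by about 4%, 13% and 28% at r = 0.3, 0.5 and 0.7. It gains about 1% at 0.2 and loses about 1% at 0. The change score is less precise than the week-24 score alone whenever r is below 0.5.

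**Chance imbalance.** The standard error of the between-arm baseline difference is √(4/N): 0.26 SD at N = 60 and 0.21 SD at N = 90. With 30% lost from 60 (42 analysed) it is 0.31 SD. Given an imbalance d, the unadjusted estimate shifts by r × d and the change-score estimate by (r−1) × d. At N = 60, r = 0.5 and d = 0.26, these are +0.13 SD and −0.13 SD. The two planned summaries would then differ by 0.26 SD, against a target effect of 0.3-0.5 SD.

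**The case against.** Several points on the other side are sound.

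**The SD is not wrong.** A reader might infer that the study will hand the definitive trial an incorrect SD. The article does not support that. The raw SD is valid and, for a baseline-adjusted trial, conservative. The adjusted SD can also be recovered: with the SDs at both times and the SD of change, r = (s0² + s24² − s_change²)/(2 × s0 × s24), and the data are held anyway. At an effect of 0.3 and an assumed 80% power, the definitive total would be 350 unadjusted, against 318, 262 or 178 at r = 0.3, 0.5 or 0.7. That saving is not forfeited by this plan; it only has to be claimed at the design stage.

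**An imbalance does not carry over in full.** Only the fraction r reaches the unadjusted estimate, which is unbiased over randomisations, and its CI already allows for this variation. Baseline characteristics will be shown by arm, so a reader could see an imbalance.

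**The gain depends on an undocumented r.** The entry criterion of about 4/10 restricts the baseline range and may lower r.

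**Baseline diaries may be incomplete.** The ratings are remote, by SMS or paper, and completion is itself something the study reports. A complete-case model could lose participants.

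**The consequence is limited.** Hand pain is secondary, no formal test is planned, and no stop-go criterion uses the pain effect. It would also go too far to extend the point to FIHOA, grip strength or MENQOL, for which the article states no model.

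**The list may not be closed.** A separate analysis plan, not shown, might add baseline. That does not alter the covariate set the article states.

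These points limit the size of the problem. They do not give a reason to leave out a baseline value that is already being collected, in an analysis whose stated purpose is estimation.

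**Conclusion.** The point holds as one of efficiency and robustness, not validity. The stated covariates omit baseline pain, and the change score does not make up for it. The likely cost is a CI wider than necessary: adjustment would narrow it by about 4% to 28% for r from 0.3 to 0.7, and by about 1% or nothing at 0.2 or below. There is also a typical chance shift of about 0.13 SD at N = 60 and r = 0.5. These sizes rest on an assumed r and on equal SDs at the two times. The feasibility outcomes are untouched. The change should be made because the pain estimate and its CI are meant to inform the definitive trial and the remedy is nearly free.

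**What to change.** 1. Add the baseline 14-day mean diary score as a covariate in the week-24 hand-pain model, alongside site and joint pattern.
2. State how incomplete baseline diaries are handled so that no participant is dropped for this reason, for example by mean imputation of the baseline covariate.
3. Report the adjusted difference with its 95% CI and, as inputs to the definitive sample size, the raw SD, the residual SD and the baseline to week-24 correlation.
4. Keep the change from baseline as a description.

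The cost is a sentence or two in the analysis plan, one degree of freedom and, if r turns out to be near zero, about 1% of CI width. No new data are needed.

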### Data monitoring

A monitoring plan has been developed and will be followed throughout the study. A Trial Steering Committee (TSC) will oversee the overall conduct of the study and make recommendations on the feasibility of a full trial following completion. The TSC will comprise of invited expert members, including at least one medically qualified person, and patient representatives. A separate medically qualified Safety Oversight Clinician (SOC) (with appropriate clinical experience and independent to the study) will be appointed to safeguard the interest of the study participants. The SOC can advise the chair of the TSC at any time, if in their view, the study should be stopped due to concerns over participant safety.

Stop-go criteria for progression to a future definitive trial were predefined at the outset of the study. These were (i) recruitment of sufficient participants in a defined period (pre-specified as ≥ 30 participants across all sites in 18 months, or, proportionate to this e.g. ≥ 22 participants in 12 months); (ii) a drop-out rate of ≤ 30% of randomised individuals; and (iii) acceptability to the majority of participants, including acceptable rates of AEs. The TSC will make recommendations on the feasibility of a future definitive trial based in part, on all three of these pre-defined criteria being met.

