Much of our evidence implicating the menopause in the onset of hand OA and for estrogen as a relevant target to date is circumstantial: from epidemiological studies, observational studies and convenience data from large HRT trials. There is further insight from a recently published report (since the development of our protocol) from electronic healthcare data in UK Community Practice Research Datalink [15]. This analysis emphasises the close temporal link to menopause (the highest rates of hand OA were seen in the year after menopause), but not all women have a temporal association to menopause (approximately 60% appear to). The study suggests that those starting HRT near to their menopause gained the most benefit in terms of protection from hand OA. In this protocol, to adhere to good practice in HRT prescribing, we mandate that participants will be at least 1 year after final menstrual period, and that they have established hand OA clinically. Whether this will prove too late, either in terms of the course of their menopause and/or their disease course to effect change on symptoms is yet to be determined. That cessation of HRT appears to be associated with onset of OA in this study is further evidence for a modulatory role for these agents, which needs to be better understood. It is important to note that here, the agent will be weaned gradually over 4 weeks, rather than being stopped abruptly to reduce the chances of any symptom flare.

To our knowledge, the study is unique, aiming to build our knowledge of whether it is possible to intervene in a poorly understood area, that of menopause and related female musculoskeletal health issues. It seeks to assess a potential tailored intervention for a group with high unmet clinical need. It will also give us valuable information on the best outcomes in this particular group of women with the condition. Particular strengths of the study are its testing of feasibility and acceptability of different ways of collecting average hand pain, which is an established outcome measure, although one that was highlighted by participants in our PPI as inadequately measured. HOPE-e is designed to determine whether a large RCT treating symptomatic hand OA in post-menopausal women with estrogen therapy is feasible. The study opened to recruitment in May 2019 (IRAS ID 236463) and is anticipated to close in February 2021.

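### The 12-month recruitment threshold (22) is not proportionate to 30 in 18 months: the proportionate figure is 20, a small error in a predefined stop-go criterion

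*Protocol article*

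**What the plan says.** The article's Data monitoring section lists three criteria for going on to a definitive trial and gives their status: "Stop-go criteria for progression to a future definitive trial were predefined at the outset of the study". The first concerns recruitment. It requires at least "30 participants across all sites in 18 months, or, proportionate to this e.g". at least "22 participants in 12 months". The second limits drop-out among those randomised to 30%. The third is acceptability to most participants, including acceptable adverse event rates.

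The TSC then makes a recommendation on feasibility "based in part, on all three of these pre-defined criteria being met".

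Two other statements give context. On sample size, the Statistical analysis section says "we estimated 60–90 participants as the number required for the feasibility study", and that "a formal power calculation was not conducted". On dates, the Discussion says: "The study opened to recruitment in May 2019 (IRAS ID 236463) and is anticipated to close in February 2021". Nothing else in the article restates, explains or corrects either recruitment figure.

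**The concern.** The article supplies its own test of the 12-month figure: it should be proportionate to 30 in 18 months. It is not. A predefined cut-off needs one value for a given recruitment period, and here a 12-month period has two: the one obtained by applying the stated rule, and the one printed as its example.

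What is at stake is whether criterion (i) counts as met when recruitment is close to the bar. Recruitment is among the primary feasibility outcomes, and the purpose of fixing such a criterion in advance is lost if someone must choose between two versions after the count is known.

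**Working it through.** **Inputs** (all from Data monitoring): at least 30 participants in 18 months; at least 22 in 12 months; the second described as proportionate to the first.

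**Step 1. Try to reproduce the plan's figure.** Direct proportion gives 30 × 12/18 = 20 exactly, so no rounding is involved. The printed 22 is not reproduced.

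**Step 2. Compare the rates.**
- 30/18 = 1.67 per month.
- 22/12 = 1.83 per month, which is 22/20 = 1.10 times the first.
- Scaled to 18 months, 22 becomes 22 × 18/12 = 33.
- At 30/18 per month, reaching 22 takes 22/(30/18) = 13.2 months.

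**Step 3. Look for a convention that would give 22.**
- Weeks: 30 × 52/78 = 20.0.
- Days: 30 × 365/548 = 19.98.
- A start-up lag of s months with no recruitment, 30 × (12 − s)/(18 − s): 19.4 for s = 1, 18.75 for s = 2, 18.0 for s = 3. A lag moves the figure further from 22.
- Slowing recruitment: 22 in the first 12 months leaves 30 − 22 = 8 for the last 6, or 1.33 per month after 1.83. That would make the pair compatible, but it is not proportionality, and the article gives no such reason.

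**Step 4. Find the counts that are affected.**
- At 12 months: 20 or 21 recruits meet the proportionate rule and fail the printed example.
- At 18 months: 30, 31 or 32 recruits meet the printed 18-month rule, but at a rate below that of the 12-month example.

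**Step 5. Gauge how often this would matter.** Assume Poisson accrual at a constant true rate, so that the 12-month count has mean 12 × rate. The two versions disagree when the count is 20 or 21.

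| True rate per month | P(≥ 20 in 12 months) | P(≥ 22 in 12 months) | Difference |
|---|---|---|---|
| 1.50 | 0.349 | 0.201 | 0.148 |
| 1.67 (30/18) | 0.530 | 0.356 | 0.173 |
| 1.83 (22/12) | 0.694 | 0.528 | 0.166 |
| 2.00 | 0.820 | 0.686 | 0.134 |

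For comparison, at a true rate of 30/18 the chance of meeting the 18-month rule, P(≥ 30 in 18 months), is 0.524. This is close to the 0.530 for 20 in 12 months and well above the 0.356 for 22 in 12 months.

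**The case against.** The case against giving this much weight is good on most counts.

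*The decision is not mechanical.* A reader might infer that two participants could turn a go into a no-go. The document does not support that. The TSC recommendation rests only in part on the criteria, and the third criterion is itself a judgement. What the discrepancy can change is whether criterion (i) is recorded as met.

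*The rule is anchored on 30 in 18 months.* A reader might infer that the printed example would be used to scale to other periods. May 2019 to February 2021 is about 21 months, so scaling from 22 in 12 would give 38.5 rather than 35 (at 15 months, 27.5 rather than 25). But the text makes other periods proportionate to 30 in 18 months and introduces 22 only as an example. Nothing in it says to scale from the example. The same dates also make it uncertain that a 12-month count will be the one applied.

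*The error is on the strict side and the band is narrow.* Using 22 would not wrongly favour progression, and only two counts at 12 months change status. Against a target of 60 to 90 participants, 20 or 21 is low on either version, although the article does not tie that target to a 12-month period.

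All of this limits the consequence. None of it makes 22 proportionate to 30 in 18 months. Nor can an analysis plan that is not shown do so, because the contradiction lies within one printed sentence.

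**Conclusion.** The arithmetic error is certain and rests on no assumption: the proportionate 12-month threshold is 20, and 22 in 12 months corresponds to 33 in 18. The printed example is 10% above the rate it is meant to illustrate.

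The consequence is small. Criterion (i) is ambiguous only for 20 or 21 recruits at 12 months. The chance of landing there is about 0.17 at a true rate of 30/18 per month, and 0.13 to 0.17 for true rates from 1.5 to 2.0. Those probabilities assume constant-rate Poisson accrual, which the article does not state. No treatment estimate or planned analysis is affected.

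It is tempting to conclude that 22 is the wrong figure and that the bar is simply too high. The document does not show that: 30 could equally be the slip. This is a small error in a predefined decision threshold that should be put right, not a flaw in the design.

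**What to change.** Before the TSC makes its recommendation, the sponsor should check its records for the figure set at the outset, say which one governs, and state a single consistent rate:
- at least 30 in 18 months with at least 20 in 12 months; or
- at least 33 in 18 months with at least 22 in 12 months.

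Any other recruitment period should be scaled from that one rate. The choice should follow the record of what was predefined and not the accrual seen so far. Recruitment opened in May 2019, so picking a version by its result would be a post hoc change to the criterion.

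The cost is one corrected figure, repeated wherever the criterion is restated, and a short note to the TSC. No participants, visits or analyses are affected.
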